## Methods

### Overview

This multistage study aims to (1) better understand the relationship between social media and women’s sexual and reproductive health in Aotearoa New Zealand and (2) meaningfully engage with stakeholders and community groups to interpret the findings and propose solutions to identified problems.

This cross-sectional, mixed methods research will be conducted over 24 months in three stages: (1) online data collection, (2) presentation of findings to stakeholders, and (3) pilot focus groups and interviews. This paper addresses the primary stage of data collection (online data collection) and follows the Checklist for Reporting Results of Internet E-Surveys (CHERRIES) checklist [27].

### Survey Design

The survey (Multimedia Appendix 1) targets women living in Aotearoa New Zealand who have used or use social media resources or communities to access information about sexual and reproductive health care. The survey draws from a convenience sample and asks for respondents who have ever identified or currently identify as women, and/or who were assigned female at birth. The survey asks for respondents who are aged 18 years or older, fluent in English, and live anywhere in Aotearoa New Zealand. The survey does not incorporate the ability to check for duplicate responses; nor does it have strict access controls. We recognize that this may impact the veracity of the results as a stand-alone dataset, but as this online survey is intended to be part of a 3-pronged approach collecting multimodal data, we believe that the data collected will be relevant and valuable in conjunction with the focus groups and individual interviews with known, recruited participants.

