#### Survey Administration

The study used a web survey hosted on a static webpage by the University of Auckland via the Qualtrics XR platform (Qualtrics LLC). The University of Auckland hosts a number of surveys, and each survey includes a standardized information page regarding the research being conducted, as well as links to contact researchers. This research relied on outreach (detailed above in the *Recruitment Process* section) to bring visitors to the University of Auckland survey page. The survey was voluntary and questions were not randomized. The survey was open from July 1, 2024, to February 15, 2025. No monetary incentives were offered for participation in the online survey, but respondents were offered a 1-page summary report of the survey results.

Adaptive questions were used to determine participant eligibility (via self-reporting) but were not used throughout the remainder of the survey. There were a total of 24 questions (including eligibility and consent questions; 19 if these are excluded) across 14 screens. No single screen had more than 4 questions, and questions that were grouped together were related. There was no completeness check conducted for participants before submitting. Respondents were able to reassess questions via the use of a back button.

Regarding the response rate, approximately 500 responses were recorded, of which approximately 320 were complete and indicated that the eligibility requirements were met. Four responses were identified as chatbot responses based on one or more indicative signals (eg, part of the question was included in the answer, which indicates a chatbot response in the experience of the research team, or text from the chatbot tool identifying itself as a chatbot was included). This survey did not control for multiple entries from the same individual at point of collection.

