### Stage 3: Focus Group and Interview Guide and Pilot Focus Groups and Interviews

Based on the results of the survey and the stakeholders’ engagement, a research approach and focus group and interview guide will be developed and piloted with approximately 5 to 8 participants. The authors acknowledge this will require an amendment to existing ethics approval. The aim of stage 3 is not to reach qualitative data saturation but to confirm a research approach and focus group and interview guide for an in-depth qualitative study in the future. Focus groups and interviews will be offered in English and te reo Māori and will be audio-recorded and transcribed verbatim. Focus groups and interviews conducted in te reo Māori will undergo forward and backwards translation into English by a certified University of Auckland or University of Waikato translator. Interview participants will be sent copies of their interview transcript, and they will have 2 weeks to edit or add to the written version of the transcript.

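### Repeat or restarted entries in the open survey can be counted more than once, and the interviews and focus groups offered in answer cannot reveal or correct this

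*Protocol article*

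**What the plan says.** All references are to the protocol article.

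- **No control at entry.** Survey Design: "The survey does not incorporate the ability to check for duplicate responses; nor does it have strict access controls". Survey Administration repeats it: "This survey did not control for multiple entries from the same individual at point of collection". The survey was open and voluntary.
- **The consequence is conceded.** Survey Design: "We recognize that this may impact the veracity of the results as a stand-alone dataset". The same sentence then turns to the other stages and calls the data "relevant and valuable in conjunction with the focus groups and individual interviews with known, recruited participants".
- **What those interviews and focus groups are.** Stage 3 says that a "focus group and interview guide will be developed and piloted with approximately 5 to 8 participants". Its purpose is limited: "The aim of stage 3 is not to reach qualitative data saturation but to confirm a research approach and focus group and interview guide", for a later in-depth study.
- **Who is analysed.** The Analysis section keeps all responses given after consent, whether or not the survey was finished. Survey Administration reports about 500 responses, of which about 320 were complete and indicated eligibility.
- **Checks that do exist.** Atypical timestamps are flagged and judged in context (Analysis). Four chatbot responses were identified (Survey Administration), and responses clearly pasted from an AI tool are excluded (Discussion).
- **Use of the results.** The quantitative analysis is descriptive and is not meant to generalise (Analysis). Early survey results are nevertheless to be published, with an acknowledgement that the later stages will add to their understanding (Results Dissemination).

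**The concern.** A descriptive survey reports how many people said what. That reading needs one record per person, and nothing in the plan secures it. Two features make repeats plausible without any bad intent. Access was open, and the inclusion rule keeps partial records, so someone who abandons the survey and later starts again leaves two records that both count for every item answered twice.

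Repeats inflate the headcount. They can shift percentages and can make one person's account look like several in the free text that goes into the thematic analysis. The article sees the veracity problem, but the only thing it sets against it is a later stage that does not bear on it. A reader of the early results could take the issue as dealt with when it remains open.

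**Working it through.** The article gives no duplicate rate and no sample-size derivation, so there is no stated figure to reproduce. The check has three parts.

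**1. Can stage 3 bear on duplicates?**

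- The survey is anonymous (Abstract, Methods).
- Email addresses are separated from responses before the team has access (Data Protection).
- No step connects a stage 3 participant to a survey record.

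Without that link, interviews cannot show whether two records came from one person, whatever the number interviewed. This is the decisive point; the size of stage 3 is secondary.

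On size:

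- Against about 500 responses: 5/500 = 1.0% to 8/500 = 1.6%.
- Against about 320 complete and eligible responses: 5/320 = 1.6% to 8/320 = 2.5%.

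Suppose, generously and against the text, that stage 3 were a random sample linked to survey records. The chance of meeting at least one repeat submitter is 1 − (1 − d)^n, with d the assumed share of repeat submitters:

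| d (assumed) | n = 5 | n = 8 |
|---|---|---|
| 1% | 4.9% | 7.7% |
| 5% | 22.6% | 33.7% |
| 10% | 41.0% | 57.0% |

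Finding none would leave an exact one-sided 95% upper bound of 1 − 0.05^(1/n): 45.1% for n = 5 and 31.2% for n = 8. Even on this favourable assumption, stage 3 would say almost nothing about the rate.

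**2. Do the existing checks catch duplicates?**

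The timestamp rule looks for unusual speed or submission outside the expected period. A restart at normal speed within the survey window meets neither example. The AI exclusion looks for machine-written text. Neither compares one record with another.

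**3. How large could the effect be?**

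Let d be the share of records that are repeats, p the true share endorsing an item, and q the share among the repeats. The observed share is (1 − d)p + dq, so the shift is d(q − p).

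- If repeats answer like everyone else (q = p), the expected shift is zero; only the headcount is wrong.
- If all repeats give the same answer (q = 1 or q = 0) and p = 50%, the shift is d/2 either way.

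| d (assumed) | Repeats in 500 | Repeats in 320 | Observed share when true share is 50% |
|---|---|---|---|
| 2% | 10 | about 6 | 49% to 51% |
| 5% | 25 | 16 | 47.5% to 52.5% |
| 10% | 50 | 32 | 45% to 55% |

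The percentages do not depend on whether 320 or 500 is used. The number finally analysed is not stated. Because partial records are kept, it can exceed 320.

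**The case against.** The strongest reply is that the article neither hides the weakness nor claims to have cured it. Survey Design offers the later stages as a reason why the data stay useful in a mixed methods study. A reader might infer that stage 3 is put forward as validation of the survey, or as the reason why no check was built; the wording supports neither. Stage 2, in which stakeholders help to interpret the findings, is also part of the design. The analysis is descriptive and is not meant to generalise, and no payment was offered for the survey, which removes one motive for repeat entry. All of this stands and limits the weight of the point.

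It would also be wrong to say that nothing is checked after collection: the timestamp and chatbot reviews exist. Nor does the text show that an email match can still be made. It speaks only of addresses that were provided, does not say that all respondents gave one, and describes them as already separated from the responses.

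Finally, the phrase about the point of collection leaves room for a later screen, and an article may leave cleaning detail to a fuller plan. That answers a complaint of missing detail. It does not answer this one, which is that the inclusion rule as written counts repeats and that the stated reply to the conceded problem does not address it. Interpretation by stakeholders cannot separate one person's two records either.

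**Conclusion.** The point holds in a limited form. Followed as written, the plan lets repeat and restarted entries count more than once, has no rule that would find them, and answers the conceded veracity problem with a pilot that cannot bear on it.

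The size is unknown. The range of about 1 to 5 points rests on assumed duplicate rates of 2% to 10%, a true share of 50%, and every repeat giving the same answer. For these rates and this true share, that is the extreme case, and repeats that resemble other respondents would shift percentages little. The documents do not show that duplicates occurred, that they dominate any subgroup, or that the survey results are invalid, and none of that should be inferred. What is at stake is moderate: the accuracy of published counts and the apparent number of voices behind a theme.

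**What to change.** **In Analysis, before any analysis is run, add a post-collection duplicate screen:**

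1. Flag identical or near-identical response patterns and verbatim-repeated free text, using timestamps to judge whether entries belong together.
2. Use platform metadata, or an email match made by the data custodian that passes on only a flag, solely if these are still available and permitted.
3. Of linked entries keep the most complete one, and the first if they are equally complete. Always keeping the first could discard a finished survey in favour of an abandoned start.
4. Report the number flagged, and show the main descriptive table with and without the flagged records.

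**In Survey Design,** replace the suggestion that the focus groups and interviews offset the veracity concern with a plain statement that repeat entries could not be prevented, followed by a reference to the screen.

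**Cost.** The core of the screen uses responses already collected and needs no new contact with participants. Since early analysis is mentioned, any tables already drafted would have to be rerun. A few genuine look-alike responses may be flagged, and partial records with few answers are the most likely to match by chance; the with-and-without table shows how much this matters.

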### Ethical Considerations

#### Institutional Review Board Approval

This survey was approved by the Auckland Health Research Ethics Committee on June 28, 2023, for 3 years. The approval was amended on July 1, 2024, to expand the survey (AH25633).

#### Informed Consent

Participants were provided with a participant information sheet standard to the University of Auckland amended to reflect the specific aims of this research. Participants provided electronic authorization of their consent to participate at the beginning of the survey.

#### Data Protection

Survey responses are held securely at the University of Auckland. Email addresses provided are decoupled from survey responses prior to access by members of the research team. All storage complies with local data security guidelines, and data will be destroyed after 10 years.

#### Compensation

Each focus group and interview participant will receive an NZ $50 (US $28.93) supermarket voucher as *koha* (gift) as a token of acknowledgment for their contribution to the research. Compensation was not provided for completion of the online survey.

### Development and Pretesting

Development and testing of the survey occurred in 2020-2021 as part of a bachelor of nursing (honors) project. This is detailed in the thesis of author HP [26].

### Stage 1: Online Survey

#### Recruitment Process and Description of the Sample Having Access to the Questionnaire (Contact Mode and Advertising the Survey)

The online survey was an open survey. Participant recruitment occurred through posts from the social media platforms of the Universities of Auckland and Waikato (Figure 1). Funding was allocated to push recruitment among specific population groups that are often underrepresented in online research; these groups are the focus of this study. Physical advertisements of our research were displayed on or in local community notice boards, coffee shops, gyms, libraries, local *marae* (communal and sacred meeting spaces), beauty salons, toilets, and supermarkets nationwide. The physical advertisement is shown in Figure 2. The researchers identified organizations invested in sexual and reproductive health care for sharing digital or poster recruitment flyers. These organizations were recruited as community partners as part of research outreach conducted by members of the research team.

**Figure 1 figure1:**
[figure not shown]
Social media participant recruitment advertisement. The image does not show participants in this study. Image source: Leinio’s Team via Canva.com.

**Figure 2 figure2:**
[figure not shown]
Physical participant recruitment advertisement. The image does not show participants in this study. Image source: Leinio’s Team via Canva.com. Social media logos sourced via images from rawpixel.com on Freepik.

#### Survey Administration

The study used a web survey hosted on a static webpage by the University of Auckland via the Qualtrics XR platform (Qualtrics LLC). The University of Auckland hosts a number of surveys, and each survey includes a standardized information page regarding the research being conducted, as well as links to contact researchers. This research relied on outreach (detailed above in the *Recruitment Process* section) to bring visitors to the University of Auckland survey page. The survey was voluntary and questions were not randomized. The survey was open from July 1, 2024, to February 15, 2025. No monetary incentives were offered for participation in the online survey, but respondents were offered a 1-page summary report of the survey results.

Adaptive questions were used to determine participant eligibility (via self-reporting) but were not used throughout the remainder of the survey. There were a total of 24 questions (including eligibility and consent questions; 19 if these are excluded) across 14 screens. No single screen had more than 4 questions, and questions that were grouped together were related. There was no completeness check conducted for participants before submitting. Respondents were able to reassess questions via the use of a back button.

Regarding the response rate, approximately 500 responses were recorded, of which approximately 320 were complete and indicated that the eligibility requirements were met. Four responses were identified as chatbot responses based on one or more indicative signals (eg, part of the question was included in the answer, which indicates a chatbot response in the experience of the research team, or text from the chatbot tool identifying itself as a chatbot was included). This survey did not control for multiple entries from the same individual at point of collection.

#### Analysis

To prepare the results of the survey for preliminary analysis and stage 2 of the research, an inclusive approach will be used with incomplete survey questions. After informed consent is provided, all responses will be included, even if the entire survey is not complete. This inclusive approach ensures that all available data contribute to the analysis, enhancing the representativeness of participant experiences and reducing response bias. Given the voluntary nature of participation and the potential for survey fatigue or partial completion, excluding incomplete responses could disproportionately exclude certain groups or perspectives. Including partial data supports equity in research by valuing all contributions and allows for more robust descriptive and exploratory analysis, particularly in early-stage or qualitative-informed research.

As we anticipate that only descriptive statistics will be feasible for the survey data, advanced statistical corrections or inferential analyses are not required at this stage. This is appropriate given the exploratory nature of the study and the likelihood of incomplete responses. The primary objective is to identify patterns and trends in the data to inform stage 2 of the research, rather than to draw generalizable conclusions. Descriptive analysis allows for meaningful insights while respecting the limitations of the dataset.

Questionnaires submitted with an atypical timestamp (eg, unusually fast completion times or submissions outside expected timeframes) will be flagged and reviewed for quality assurance. These cases will not be automatically excluded, but rather assessed contextually to determine if the data appear valid and consistent with other responses. This approach ensures that we do not inadvertently exclude legitimate responses from participants who may complete the survey quickly due to familiarity with the content, while still maintaining data integrity.

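### Agreement with other responses is a criterion for judging timestamp-flagged questionnaires, so any exclusion after review can depend on answer content and shift results toward common answers

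*Protocol article*

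**What the plan says.** All of the rule stands in the Analysis subsection of Stage 1.

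- Trigger: "Questionnaires submitted with an atypical timestamp (eg, unusually fast completion times or submissions outside expected timeframes) will be flagged and reviewed for quality assurance".
- Consequence: "These cases will not be automatically excluded"; instead they are "assessed contextually to determine if the data appear valid and consistent with other responses".
- Stated purpose: "This approach ensures that we do not inadvertently exclude legitimate responses from participants who may complete the survey quickly due to familiarity with the content".

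The same subsection opens with a broad inclusion rule: "After informed consent is provided, all responses will be included, even if the entire survey is not complete". It gives as a reason that "excluding incomplete responses could disproportionately exclude certain groups or perspectives".

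The recruitment subsection says that funding was used to reach "specific population groups that are often underrepresented in online research; these groups are the focus of this study".

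**The concern.** A quality check should separate genuine records from spurious ones. Agreement with other respondents does this poorly in both directions. A genuine respondent with an unusual experience who finishes quickly could fail it. A repeat entry by the same person, or an automated entry giving typical answers, could pass. The second weakness matters here because the survey had no duplicate check or strict access controls (Survey Design) and no attention-check questions (Discussion). Some automated entries are caught separately: four were identified by chatbot signals (Survey Administration).

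If a flagged record is dropped because it disagrees with the rest, inclusion depends on the answer being summarised. Variation then shrinks and apparent consensus grows. Descriptive percentages are exposed to this as much as a test would be. The qualitative survey answers also go into thematic analysis (Data Analysis), where losing a few divergent accounts could thin out or remove a theme. The survey results are then used to set priorities for the interviews and focus groups (Results Dissemination), so a lost perspective could carry forward.

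**Working it through.** **Step 1: does the text allow exclusion on this ground?** There is no explicit removal rule. But saying that cases are assessed rather than excluded automatically, with the aim of not losing legitimate responses by accident, makes sense only if a case that fails the assessment can be excluded. Exclusion is therefore implied.

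**Step 2: who are the other responses?** Survey Administration uses the word for whole submissions: "approximately 500 responses were recorded, of which approximately 320 were complete and indicated that the eligibility requirements were met". The sentence at issue is about whole questionnaires. Comparison with other respondents is thus the more natural reading, though not the only one.

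**Step 3: does it fit the rest of the subsection?** The inclusion rule takes all consented responses, and its rationale warns about losing groups or perspectives through exclusion of incomplete records. A consistency criterion carries the same risk for flagged records.

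**Step 4: how large could the shift be?** The article gives no figure to reproduce. The inputs below are all assumptions:

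- m = true share giving a minority answer (10%, 20%, 30%)
- f = share of questionnaires flagged, unrelated to the answer (2%, 5%, 10%, 20%)
- r = share of flagged minority-answer records removed (0.5 or 1), with no flagged majority-answer record removed

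Observed minority share = m(1 - f·r) / [m(1 - f·r) + (1 - m)]. The number of records cancels out, so it does not matter here whether the base is about 320 or about 500.

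Example: m = 0.20, f = 0.10, r = 1 gives 0.18 / (0.18 + 0.80) = 18.4%, a shift of -1.6 points.

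Observed share (shift in points) at r = 1:

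| m | f = 2% | f = 5% | f = 10% | f = 20% |
|---|---|---|---|---|
| 10% | 9.8% (-0.2) | 9.5% (-0.5) | 9.1% (-0.9) | 8.2% (-1.8) |
| 20% | 19.7% (-0.3) | 19.2% (-0.8) | 18.4% (-1.6) | 16.7% (-3.3) |
| 30% | 29.6% (-0.4) | 28.9% (-1.1) | 27.8% (-2.2) | 25.5% (-4.5) |

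The smallest shift in the range is at m = 10%, f = 2%, r = 0.5: 0.099 / (0.099 + 0.90) = 9.91%, or -0.1 points. The largest is at m = 30%, f = 20%, r = 1: 0.24 / (0.24 + 0.70) = 25.5%, or -4.5 points.

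**Step 5: sensitivity to the one-sided assumption.** If half of the flagged majority-answer records are removed as well (m = 0.20, f = 0.10, all flagged minority records removed), the share is 0.18 / (0.18 + 0.80 × 0.95) = 0.18 / 0.94 = 19.1%, a shift of -0.9 points. If removal is equally likely for both answers, the share stays at m. For m = 20% it is 20.0% at f = 5% and at f = 20%.

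In the other direction, suppose minority-answer respondents were flagged at 2f, again with m = 20% and all their flagged records removed. The share would be 18.4%, 16.7% and 13.0% at f = 5%, 10% and 20%. The article gives no reason to think that flagging is related to the answers, so this is a bounding case only.

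**The case against.** The strongest reply is that the article never says a record will be removed for disagreeing. It says the opposite of automatic exclusion, its purpose is to protect fast completers, and apparent validity is a separate criterion beside consistency. Being consistent with other responses could mean a plausible pattern of completion, or coherence with the same person's other answers, rather than agreement with majority opinion. The survey is a convenience sample, summarised descriptively, with no aim to generalise, and no test depends on a shift of a few points.

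Much of this stands. Removal is an implication, the wording is ambiguous, and the rule touches only flagged records. These points limit severity. They do not rescue the wording: a criterion is stated, its natural reading compares respondents with one another, and if something else was meant the sentence should say so.

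Four stronger readings are tempting, and the documents do not support them.

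- *A reader might infer that the review will favour the anticipated finding*, since the abstract reports early analysis and an expected confirmation of the hypothesis. Nothing shows that minority answers oppose the hypothesis or that fast completers hold minority views. The direction shown is toward common answers only.
- *A reader might infer that the trigger for submissions outside the expected period is empty in an open survey.* It is not: Survey Administration gives an opening window of July 1, 2024 to February 15, 2025.
- *A reader might count the missing numeric cut-off for fast completion as a defect.* A condensed article commonly leaves such detail to the full plan, so it is not one.
- *A reader might take a marked fall in minority shares as the expected result.* That would need a high flag rate and complete, one-sided removal, neither of which is documented.

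**Conclusion.** The concern holds in a limited form. The Analysis subsection makes agreement with other responses a ground for judging flagged questionnaires. If records are excluded on it, inclusion depends partly on answer content and any shift runs toward common answers. This conflicts with the subsection's own case for inclusiveness and with the attention to underrepresented groups. Under the assumptions in Step 4 the shift is about -0.1 to -4.5 percentage points. The true size cannot be known until the number flagged and the number removed are reported. Severity is minor to moderate: the wording should be corrected, but the study does not stand or fall on it.

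**What to change.** In the Analysis subsection of Stage 1:

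1. Delete the part of the criterion that asks whether the data agree with other responses, and keep the assessment of validity.
2. Base that assessment on signals that do not depend on agreement with other respondents' views: completion time, duplicate or copied text, chatbot text, and contradictions within the same questionnaire. Some of these require reading the answers, but none counts an unusual opinion against the respondent.
3. Keep the trigger for submissions outside the expected period, and tie it to the July 1, 2024 to February 15, 2025 window.
4. Report how many questionnaires were flagged and how many removed.
5. Show the main descriptive tables with and without all flagged records.

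Collection has closed and some data have been analysed, so the rule cannot be fixed blind to every answer. The review is still described in the future tense, so the rule can be written down before it is applied. The cost is a short rewording and one extra table. A few low-quality records may stay in the main tables, and the comparison in item 5 will show how much the flagged records matter.
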